### WP2: Short and long‐term causal effects of compulsory inpatient and outpatient mental health care, including administration of medication without consent

3.2

The main objective of WP2 is to estimate the causal effect of compulsory mental health care on health and social functioning outcomes for people with SMI, potentially including long term costs to the public purse and society associated with these differences. We will use variation in clinical practice among catchment areas as IV to estimate the causal effect of compulsory care on multiple outcomes (see Figure 5). The primary analyses will be restricted to (a) people with SMI; and (b) people who are referred to compulsory inpatient mental health care.

We expect that patients on the margin of compulsory care after discharge will be treated differently depending on whether they live in areas with higher or lower tendency to use OC. Since OC is most often used to ensure medication compliance (Riley et al., 2019) and almost all people on OC receive antipsychotic treatment (Barkhuizen et al., 2020; Riley et al., 2019; Rugkåsa et al., 2015), we will use provider preference for use of OC as a proxy to measure the effect of administration of medication without consent. This WP will also test assumptions that must be fulfiled for IV‐estimates to credibly reflect causal relationships (Widding‐Havneraas et al., 2021).

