### The purpose of compulsory care

1.1

The purpose of compulsory mental health care is to reduce the short‐term risk of suicide or self‐harm and reduce the risk that the person will be a victim or perpetrator of violence or acts that violate others' life, health, or freedom. In the long term, mental health care, including compulsion, is expected to facilitate recovery and prevent relapse. Improved outcomes can potentially impact beyond health and risks of harm, to influence educational attainment; employment and welfare reliance; relationships and childcare; and criminal justice involvement.

The relationship between inpatient and outpatient compulsory care remains unclear. As both are imposed on patients without their consent, it may be worthwhile to examine these practices together.

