### WP1: The epidemiology of severe mental illness, compulsory hospitalisation, and outpatient commitment

3.1

This WP will answer three categories of epidemiological questions concerning people in contact with specialist mental health or addiction services in Norway in 2015–2016.

The first category will compare short and long‐term trajectories of persons with and without SMI in voluntary and compulsory care. Additionally, the outcomes of these persons will be compared to a control group from the general population.

The second category will describe the extent of geographical variation inPrevalence of SMI.All mental health service use for people with SMI, including referrals to specialist mental health care and per‐person use of antipsychotic medication.Compulsory inpatient and outpatient health service use.

We will test the competing hypotheses that providers who are less likely to use one form of compulsion may be more likely to use the other, or that providers who use little inpatient compulsion also tend to use little OC.

Data will be aggregated to geographical regions, specifically catchment areas to community mental health centres, based on residency. The variation will be described as population‐based rates and as the proportion of inpatients and outpatients with a compulsory referral or legal status. The relationship between urbanicity and risk of psychosis (Fett et al., 2019) has not previously been documented in Norway, but will also be covered in WP1.

The third category will explore associations between rates of compulsory care per population and indicators of social inequality and socio‐economic position in the catchment areas, such as the proportion of high school dropouts; median income in the area; and unemployment rate.

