### The Norwegian legal framework

4.4

Individuals must be evaluated by a physician before being referred to inpatient compulsory mental health care. After arrival in hospital, a psychiatrist or specialist psychologist must re‐evaluate the patient within 24 h. Figure 6 shows Norway's legal framework for administrative compulsory mental health care.^2^ §3.2 governs compulsory observation, which can last up to 10 days and be extended 10 days §3.3 regulates compulsory inpatient and outpatient mental health care, which requires a severe mental illness, a treatment criterion (their prospects of recovery will be significantly reduced, or their condition will deteriorate significantly, without compulsory care) or danger criterion (the person constitutes a serious and immediate risk to the life or health of self or other). In cases not involving danger, the person must also lack decision‐making capacity. Medication without consent is only permitted for those in compulsory care and requires additional formal decisions.

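### WP2 labels an outpatient-commitment instrument as measuring medication without consent; it identifies at most the effect of the outpatient-commitment package for marginal patients

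*Protocol article*

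**What the plan says.** Section 3.2 (WP2) plans to use variation between catchment areas as an instrumental variable. For medication it commits as follows: "we will use provider preference for use of OC as a proxy to measure the effect of administration of medication without consent". Two reasons are given: "OC is most often used to ensure medication compliance", and "almost all people on OC receive antipsychotic treatment". The title of WP2 also names this medication effect as one of its targets.

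Section 4.4 (The Norwegian legal framework) describes the treatment itself: "Medication without consent is only permitted for those in compulsory care and requires additional formal decisions". It also says that section "3.3 regulates compulsory inpatient and outpatient mental health care".

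Section 1 (Introduction) describes OC as a legal means of making people receive outpatient services. On how the two forms of compulsion relate, section 1.1 says "The relationship between inpatient and outpatient compulsory care remains unclear". Section 3.1 (WP1) sets two rival hypotheses to be tested. One is substitution: "providers who are less likely to use one form of compulsion may be more likely to use the other". Under the other, the two forms go together, and a provider low on one is low on both.

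Section 5.2 requires that the instrument reach the outcome only through the treatment. It plans to test this in a control group with no contact with mental health services.

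**The concern.** The treatment named in the target (medication without consent) is not the treatment that the instrument moves (OC). The two reasons in WP2 concern the purpose of OC and the receipt of antipsychotics. Neither gives a rate of formal decisions on medication without consent, or shows how much higher that rate is on OC than among comparable patients not on OC.

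What is at stake is the meaning of the result. The Discussion foresees use of the findings in policy and legislation for each of three scenarios: no difference, better outcomes or worse outcomes. A null OC estimate reported under the medication label could be read as showing that medication without consent does nothing. A non-null estimate could be credited to medication when it came from compelled contact or legal status.

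**Working it through.** The article states no effect size, rate or power figure for this analysis, so there is no figure to reproduce. The check has two parts.

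**1. The sections side by side**

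- Is OC the named treatment? By section 4.4, compulsory care is necessary for medication without consent but not sufficient, because further decisions are required.
- Is OC its only setting? No. Medication without consent is permitted in compulsory care, and the same paragraph of the Act covers inpatient and outpatient care.
- Does OC act only through medication? By the Introduction, OC compels outpatient services. With medication as the treatment, that is another route to the outcome.
- Can the planned test see this? The negative controls have no service contact. They experience neither OC nor inpatient compulsion, so a null result in them is uninformative about either route.
- Does the argument in section 5.2 that everyone assigned to treatment receives it carry over? It is made for compulsory care. Given section 4.4, it does not extend to medication.
- Does the reduced-form fallback in section 5.2 rescue the label? It estimates the effect of area preference, which is again not the effect of medication.

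**2. What the instrumental-variable ratio estimates**

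Let area OC preference and area inpatient preference be standardised with correlation rho, and let them move the shares on OC and in inpatient compulsion by s_O and s_I. Let OC raise medication without consent by d per OC patient. Let b_M be the effect of that medication, b_O the effect of the rest of OC, and b_I the total effect of inpatient compulsion. Then

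Cov(Y, Z_O) / Cov(OC, Z_O) = d·b_M + b_O + rho·(s_I/s_O)·b_I.

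Apart from chance cancellation, this equals b_M only if d = 1, b_O = 0 and rho·b_I = 0. The documents establish none of the three, and section 4.4 speaks against d = 1.

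All values below are assumptions, with s_I = s_O. First, a true medication effect of zero with d = 0.5:

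| b_O | b_I | rho = -0.5 | rho = 0 | rho = +0.5 |
|---|---|---|---|---|
| 0 | -0.05 | +0.025 | 0 | -0.025 |
| -0.05 | 0 | -0.05 | -0.05 | -0.05 |
| -0.05 | -0.05 | -0.025 | -0.05 | -0.075 |

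Entries are per OC patient. Dividing by d = 0.5 to express them per medicated patient doubles each one, so the second row becomes -0.10 although the true effect is zero.

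Second, a true medication effect of -0.10 with no other route. The estimate is d × (-0.10): -0.10, -0.07, -0.05 and -0.03 for d = 1, 0.7, 0.5 and 0.3.

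A simulation with 200,000 areas agreed with these values to within rounding. Adjusting for inpatient compulsion at area level removed the rho term in every case. It left b_O in place (still -0.05 in the second and third rows) and did not undo the scaling by d.

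**The case against.** The article openly calls the measure a proxy, gives its reasons, and promises to test the instrumental-variable assumptions. Medication is an addition to the main objective of WP2, which is the effect of compulsory care, so the main analyses do not depend on this label. If OC acted only through medication and rho·b_I were zero, the proxy would keep the right sign and merely be attenuated. These points limit the damage. They do not make the stated target the one that is estimated, and no test described in the article addresses the medication proxy.

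Several stronger readings are tempting but unsupported:

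- A reader might infer that OC preference cannot be separated from inpatient preference, or that WP1 expects them to be correlated. Sections 1.1 and 3.1 leave the relation open and rho = 0 is not excluded. Table A1 lists involuntary admission and OC as separate variables, so both preferences can be constructed.
- A reader might infer that OC preference will be used with no account taken of inpatient preference. The article does not say so. Model form and covariates may lie in a fuller plan that is not shown.
- A reader might infer that the first stage on medication can never be checked, because Table A1 names no variable for the formal decisions. The table gives examples of variables only.
- A reader might infer that the main inpatient analysis is biased in the same way. This is not shown. The article's definition of compulsory care includes both forms, and OC that follows from a compulsory admission can be part of that admission's total effect.
- A reader might ask for a two-treatment two-stage least squares model as the primary analysis. With heterogeneous effects, such a model does not in general give a local average treatment effect for each treatment, which is the estimand that section 5.2 describes.

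**Conclusion.** The point holds for the label. As written, section 3.2 claims an effect that its instrument does not identify, and section 4.4 of the same article supplies the reason. What is identified, if the other assumptions hold, is at most the effect of the OC package for patients at the margin of OC.

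This conclusion rests on the article's text and on no assumed number. Its size cannot be derived from the document: the values under working are illustrations, with d from 0.3 to 1 and rho from -0.5 to +0.5. Leakage from inpatient compulsion is an open possibility, not an established bias. It vanishes if rho is zero, if inpatient compulsion has no effect, or if area inpatient preference is adjusted for. The mismatch between OC and medication remains in all those cases.

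**What to change.** 1. In section 3.2, its title and any conclusions drawn from it, name the estimand as the effect of OC, or of area preference for OC. Present medication without consent as a possible mechanism only, unless the formal medication decisions are obtained and the first stage of OC preference on them is reported. Even then, the route through compelled contact and legal status must be argued separately.
2. Because the relation between OC and inpatient compulsion is left open, report a sensitivity analysis of the OC estimate that adjusts for area inpatient-compulsion preference, alongside the WP1 correlation between the two preferences.

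Cost: the first change is wording and narrows the claim. The second is one further model. It leaves a share 1 - rho² of the instrument's variance, so at an assumed rho of ±0.5 that share is 0.75 and intervals widen by about 1/√0.75 = 1.15, other things equal. A stronger correlation costs more.

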## METHODS AND ANALYSIS

4

### Design

4.1

The project will use methods of description and causal inference (Hernán et al., 2019). Individual‐level data on the whole Norwegian population will be linked across multiple registries. If uncertainty remains whether conditions for IV‐analyses are met, the use of hierarchical models or inverse probability weighting might be relevant, in addition to conventional epidemiological approaches.

### Co‐creation and user involvement

4.2

Service users, including people with lived experience of compulsion, have been consulted intermittently during the project planning. We will host seminars with service users and providers to ensure that our research questions are relevant for the users and the clinical field.

### The Norwegian legal framework

4.4

Individuals must be evaluated by a physician before being referred to inpatient compulsory mental health care. After arrival in hospital, a psychiatrist or specialist psychologist must re‐evaluate the patient within 24 h. Figure 6 shows Norway's legal framework for administrative compulsory mental health care.^2^ §3.2 governs compulsory observation, which can last up to 10 days and be extended 10 days §3.3 regulates compulsory inpatient and outpatient mental health care, which requires a severe mental illness, a treatment criterion (their prospects of recovery will be significantly reduced, or their condition will deteriorate significantly, without compulsory care) or danger criterion (the person constitutes a serious and immediate risk to the life or health of self or other). In cases not involving danger, the person must also lack decision‐making capacity. Medication without consent is only permitted for those in compulsory care and requires additional formal decisions.

**FIGURE 6 mpr1980-fig-0006:**
[figure not shown]
The Norwegian Mental Health Care Act regulates compulsory inpatient and outpatient mental health care. Decisions for compulsory care are made at referral; within 24 h of admission; within 10 days (for compulsory observation); at least every third month, and 1 year after referral for compulsory mental health care, but discharge can be decided at any time.

## DATA ACQUISITION AND MANAGEMENT

5

We will receive data from nine Norwegian registries, listed in Table A1 in the appendix. The Norwegian Patient Registry (NPR) will prepare and send a population list with personal identification numbers to Statistics Norway. They will draw a control group from The Central Population Register (CPR), matched on age and gender, which is identical to the treatment group, except that they were not referred to specialist mental health or addiction services. The CPR will send the list of personal identification numbers together with a project‐specific pseudonymised number back to the NPR and to the Institute of Public Health who manages the Cause of Death registry and the Norwegian Prescription Database. Statistics Norway will keep the linkage key between the pseudonymised number and the personal identification number for future data deliveries. The remaining registries' data will be attached by Statistics Norway and sent to Haukeland University Hospital, where it will be securely stored and analysed.

### Study samples and target populations

5.1

Since the registers are mandatory, they typically contain data that is complete, reliable and representative. The project will obtain data on everyone above nine years who were referred to specialist mental health or addiction services in Norway 2015–2016. For WP1, we estimate that the patient sample and the equally sized control group from the general population will constitute approximately 600,000 individuals. For WP2 we will specify smaller target populations, with increased risk for compulsory mental health care. Relevant subgroups include people who have or will receive a diagnosis of SMI and people referred involuntarily during the study period.

The cohort period is limited to 2015–2016, but we will obtain data for both the cohort and control group for the period 2010–2025. This permits differentiation between the first episodes of SMI and patients with previous contact with specialist services.

The registry data will be supplemented with municipal data (See Table A1), which will be used to explore associations between structural and capacity‐related regional variables and rates of compulsory care and SMI. Furthermore, they can be used to adjust for different case‐mix in the catchment areas.

For both WPs it might be relevant to perform separate analyses for compulsory observation and compulsory mental health care, since the patient groups do not overlap completely and expected outcomes differ somewhat. Similarly, it can be relevant to perform subgroup analysis for some outcomes based on gender, diagnoses or other characteristics.

### Assumptions of provider‐preference instrumental variables

5.2

First, the *relevance criterion* implies that the instrument must be correlated with the treatment variable. We intend to generate IVs at the regional provider level of catchment area to Community Mental Health Centres (Ruud and Friis, 2021). Stable geographical variations in compulsory hospitalisation between catchment areas have been documented, and more than 80% of variation in ranked rates of compulsory hospitalisation per population could be predicted by the area rankings for the previous year, while 50%–75% of variation in inpatient rates could be predicted this way (Hofstad et al., 2021), suggesting that provider preference for compulsory care can be a strong instrument (Hernán and Robins, 2020).

Second, the *exclusion restriction assumption* implies the instrument should only impact the outcome through treatment. This means that service providers' preferences for using compulsory mental health care in an area should impact whether involuntary care is initiated, while being uncorrelated with outcomes through other paths. We will use a *negative control population* to test this assumption (Lipsitch et al., 2010); since provider preference should have no impact on those who were not in contact with mental health services, the impact of the instrument on the outcome should be zero in the control cohort.

Theoretically, the instrument will control for unobserved and observed characteristics of individuals that can affect the outcome. However, instrument‐outcome confounders can still bias estimates, in which case the instrument would not be equivalent to “as‐good‐as‐random assignment” (Garabedian et al., 2014). So the third *assumption of no confounding* requires that there are no unmeasured common causes of the instrument and the outcome. This will be tested indirectly through balance tests of baseline covariates (Brookhart and Schneeweiss, 2007).

The fourth assumption of *monotonicity* ensures that the estimand can be interpreted as the Local Average Treatment Effect (LATE). Individuals who clearly fill criteria for compulsory care are assumed to be subject to compulsion in all areas, while persons where compulsory hospitalisation is clearly not indicated are not subject to compulsion anywhere. Consequently, the estimand represents the effect of compulsory care for people with SMI at the margin/in the grey zone of compulsory care; individuals who are expected to be treated differently if they live in areas with a high versus a low use of compulsory care (See Figure 2). By design, we know that all people who are assigned to the treatment (compulsory care), will receive it, thereby ensuring no ‘*defiers’*.

Subject‐matter knowledge, required for all but the first assumption, will be provided by project group members, as well as service‐users and providers. Topics meriting investigation include whether the variation is random or remains stable over time. Are there differences in case mix, with different prevalence of SMI between areas? Is there risk of selection bias, where service users residing in low‐compulsion areas, but require compulsory hospitalisation, are transferred to areas that use more compulsion?

In general, people are unaware whether rates of compulsory mental health care in their catchment area are high or low compared to the country average. Given the retrospective baseline, the quasi‐experimental framework is similar to a double‐blinded experiment where neither service users nor providers could identify the treatment. While some clinicians may have recognised that the use of compulsory care tended to be higher or lower within their area, they were unaware that they partook in a natural experiment. There is also little reason to expect that people self‐selected to areas based on compulsory hospitalisation rates, thereby reducing the risk of selection bias.

Even if the exclusion restriction assumption is violated, the ‘*reduced form’* can provide an unbiased estimate of the effect of the instrument on the outcome (Chernozhukov and Hansen, 2008), and will answer whether a higher or lower propensity for compulsory care results in superior, worse or similar outcomes for patients.

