**FIGURE 3 mpr1980-fig-0003:**
[figure not shown]
Geographical variation in compulsory hospitalised patients in Europe and Norway. Average rates per 100.000 inhabitant. Map based on data from (Hofstad et al., 2021; Sheridan Rains et al., 2019).

There are likely many factors related to the services and their patient populations, that influence the varying rates of compulsory admission. Characteristics of service providers might include bed capacity and duration of hospitalisations (Bale et al., 2021); clinicians' evaluation of decision‐making capacity (Høyer et al., 2022); different attitudes to coercion, which has been shown to vary between professions (Aasland et al., 2018); varying interpretations of legal criteria (Feiring and Ugstad, 2014); availability of systematic family involvement and support for people with SMI (Hestmark et al., 2021); other local experience‐based practises, including quality of voluntary care, which can impact on whether compulsory care is considered necessary (Sharpe, 1997); or other individual differences in clinical decision‐making (Bagby et al., 1991). Variation related to case‐mix might include differing characteristics among the population‐at‐risk of compulsory care, such as age, gender, ethnicity, employment status, comorbidity and previous history of compulsion (Barnett et al., 2019; Walker et al., 2019).

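### The negative control population chosen for the exclusion restriction has little or no power against paths that run through the mental health services, so a null there should not count as support against them

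*Protocol article*

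**What the plan says.** Section 5.2 of the protocol article defines the exclusion restriction: "the instrument should only impact the outcome through treatment". A negative control population will be used "to test this assumption". The reason given is "since provider preference should have no impact on those who were not in contact with mental health services", and the expected result is that "the impact of the instrument on the outcome should be zero in the control cohort".

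Section 5 defines the controls as people drawn from the population register and matched on age and gender, "except that they were not referred to specialist mental health or addiction services".

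The instrument is the practice of the Community Mental Health Centre catchment area (section 5.2). Section 2.5 lists what may lie behind area differences in compulsory admission. On the provider side: "Characteristics of service providers might include bed capacity and duration of hospitalisations", systematic family involvement and support, and local practices "including quality of voluntary care, which can impact on whether compulsory care is considered necessary".

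The third assumption, no confounding, is to be checked by balance of baseline covariates. Section 5.2 also relies on subject-matter knowledge for every assumption but relevance, and offers the reduced form if the exclusion restriction fails. Section 4.1 names other methods if doubt about the instrumental variable conditions remains.

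**The concern.** A negative control is informative about a bias when it shares the suspected bias path and lacks only the treatment. People outside mental health services lack both: they receive no compulsory care, and they are not exposed to the voluntary care, beds, lengths of stay or family support of the local provider. For those paths, a zero in the controls follows from who the controls are, whether or not the restriction holds among patients.

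The instrument sits at provider-area level, so a tendency towards compulsion comes bundled with the rest of that provider's care. If areas with more compulsion also have better or worse voluntary care, patients' outcomes may differ for that reason, and the estimate would attribute the difference to compulsion. The Discussion draws policy conclusions from either direction of effect. False reassurance on this assumption would carry straight into them.

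**Working it through.** The document states no figure for this test, so there is nothing to reproduce. The check is by reasoning, then by illustration.

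**Which paths each group can show.** Let π be the change in compulsion per unit of the instrument, β the true effect of compulsion, g_s a path confined to the services and g_a a path that reaches everyone in the area.

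- Patients, outcome on instrument: βπ + g_s + g_a
- Controls, outcome on instrument: g_a
- Instrumental variable estimate in patients: (βπ + g_s + g_a)/π = β + (g_s + g_a)/π

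The control cohort informs on g_a. The bias depends on g_s + g_a.

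**Size of the bias from a service path (assumed inputs).** With g_s = 1 pp and g_a = 0, the bias is g_s/π:

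- contrast in compulsion 20 pp: 1 pp / 0.20 = 5 pp
- contrast 10 pp: 1 pp / 0.10 = 10 pp
- contrast 5 pp: 1 pp / 0.05 = 20 pp

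**Behaviour of the planned test (illustrative simulation, 2000 runs per setting).** All inputs are assumptions: 40, 75 or 100 areas; 400 patients and 4000 controls per area; outcome risk 15% in patients and 2% in controls; first stage of 8 pp per SD of the instrument; true effect zero; two-sided 5% test. At 75 areas, 75 × 4000 = 300,000 controls, which fits the protocol's total of about 600,000 split into two equal groups.

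Service-only path, 75 areas:

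| g_s per SD | Bias by formula, g_s/0.08 | Mean simulated estimate | Control-cohort test rejects |
|---|---|---|---|
| 0 | 0 | -0.1 pp | 5.2% |
| 0.5 pp | 6.25 pp | 6.2 pp | 5.85% |
| 1 pp | 12.5 pp | 12.5 pp | 5.5% |
| 2 pp | 25 pp | 25.0 pp | 5.5% |
| 4 pp | 50 pp | 50.1 pp | 4.95% |

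Over all three numbers of areas the rejection rate lay between 4.45% and 6.15%, which is the nominal level whatever the size of the violation.

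Area-wide path, 75 areas: with g_a of 0.1, 0.2 and 0.5 pp per SD the same test rejected in 97.6%, 100% and 100% of runs. For such paths the check works.

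Leakage, 75 areas: if 2% to 5% of the service path reached the control cohort because some controls do use services, the test rejected in 13% to 48% of runs at g_s = 1 pp and in 33% to 97% at 2 pp.

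The simulation has no area variation beyond sampling error and the modelled paths, so the area-wide and leakage power figures are optimistic. The service-only result does not depend on that.

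**Whether anything else in the plan covers g_s.** Balance of baseline covariates is assigned to the third assumption and does not test a direct effect of service features. Subject-matter knowledge is not an empirical test. The reduced form carries g_s with it and cannot separate compulsion from the other features. The methods in section 4.1 apply only if doubt remains, and a null in the control cohort could wrongly remove that doubt. Section 5.1 plans to relate capacity-related regional variables to rates of compulsory care and to use municipal data for case-mix, not to test this assumption.

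**The case against.** The strongest reply is that the test is partial, not empty. Section 5.2 words the restriction broadly enough to cover any other path from preference to outcome, and paths through the local economy, policing or emergency care would show in the general population. This stands. A reader might infer that the test passes however badly the assumption fails. That is true only of violations confined to the services.

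Second, section 2.5 lists causes of compulsion rates. It does not say that they change outcomes or act only on service users. A feature that drives both preference and outcome is a common cause, which belongs to the third assumption. This also stands, so the line between the two assumptions is not clean. It does not rescue the test: under either label the bias has the same form, and the control cohort has little or no sight of it.

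Third, a reader might infer from "which is identical to the treatment group, except that they were not referred to specialist mental health or addiction services" that people already in care can be drawn as controls, or that the claim of identity is a flaw in itself. The article gives no time window for non-referral, and the 2010–2025 data may allow earlier contact to be identified, so the first is not established. The second is secondary: the zero-effect check compares controls across areas and does not need them to resemble patients. Any leakage would give the test some unplanned power and would contradict its stated rationale.

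Fourth, the plan admits that the restriction may fail and says that Work Package 2 will test assumptions. That leaves room for a further check but does not supply one.

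**Conclusion.** The concern holds in limited form. The general-population cohort is a useful check on area-level confounding and area-wide paths. It has little or no power against paths through the mental health services, which the protocol's own list makes plausible, and a null there should not be read as support for the exclusion restriction against them. No other empirical test of those paths is described.

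That conclusion rests on who the controls are and not on any assumed number. The bias of 10 pp (range 5 to 20 pp) and all simulation results are illustrations: the documents give neither the size of a direct path nor the first-stage contrast. The documents do not show that the restriction fails, or that a service difference will be published as an effect of compulsion. They show that the named test could not warn of it.

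**What to change.** 1. Keep the general-population cohort, but state in section 5.2 that it checks area-level confounding and area-wide paths only, and that a null does not address service-level paths.
2. Add a falsification analysis in patients of the 2015–2016 cohort, in the same catchment areas, whose baseline-predicted risk of compulsion is near zero. Select them on baseline data, not on observed legal status. Regress the same outcomes on the instrument.
3. State the reading in advance. A non-zero result, set beside the general-population result, is evidence against instrument validity, through exclusion failure or confounding. A null is supportive only.
4. Report the instrumental variable estimates with and without adjustment for bed capacity, already listed in Table A1, as a sensitivity analysis.

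The cost is a change of wording, one further analysis and one sensitivity analysis, all in data the project already plans to obtain (about 300,000 patients, half of the stated 600,000). The downside is that low-risk patients share only some of the service paths and may be little exposed to acute-bed capacity or to family support for severe mental illness. Referral itself may also vary by area and bring selection into the comparison.
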